### 3. INTRODUCTION

#### 3.1. Background

Idiopathic (immune) thrombocytopenic purpura (ITP) is an autoimmune disorder affecting both children and adults; it is characterized by a low platelet count, normal results on a bone marrow examination (except possibly for increased megakaryocytes), and the absence of specific causes of thrombocytopenia, such as leukemia, aplastic anemia or disseminated intravascular coagulation [1-3]. Childhood ITP is typically of acute onset. In more than 70% of children, spontaneous and permanent remission occurs within 1 year of onset [3,4]. In contrast, the majority of adults have persistent ITP, although the natural history is less defined than that for ITP in children, and some patients do improve with time [5,6]. Rarely, life-threatening bleeding occurs, but when it does, intracranial hemorrhage is the principal cause of death [7,8]. Serious hemorrhage is most likely to occur when the platelet count falls below  $20 \times 10^9/L$  [2,3,5]. Therefore, treatment options for ITP are intended rapidly to increase the platelet count and include glucocorticoids, immune globulin intravenous (IGIV) and, in Rh(D)+ patients, intravenous anti-D (Rho) globulin [2].

The first report of the efficacy of IGIV in the treatment of ITP appeared in 1981 [9]. More than 100 studies have subsequently confirmed the safety and efficacy of IGIV as treatment of ITP in children and adults [10-15]. A substantial and rapid platelet increase can be achieved with an IGIV dosage of 1 g/kg/day repeated for 2 consecutive days and this is now preferred to the original regimen of 400 mg/kg/day repeated daily for 5 days [15-17].

GAMMAPLEX® 5% is a newly developed, highly purified, unmodified IgG product intended for intravenous (IV) administration; it is manufactured by Bio Products Laboratory (BPL), United Kingdom (U.K.) from plasma from healthy U.S. donors who are subjected to medical examinations, laboratory tests, and a review of their medical history. Each donation must be non-reactive for Hepatitis B surface antigen (HBsAg), anti-HIV-1 and HIV-2 antibodies, and anti-HCV antibodies. Furthermore, plasma minipools (512 donations per pool) undergo nucleic acid amplification/polymerase chain reaction (NAT/PCR) testing for HIV, HBV, HCV, Hepatitis A (HAV), and Parvovirus B19. Manufacturing pools are tested for HBsAg, HIV-1/2 antibodies; HCV and Parvovirus B19 are also tested using NAT/PCR.

GAMMAPLEX is a ready-prepared solution for IV administration that contains 5 g human normal immunoglobulin and 5 g D-sorbitol (as stabilizer) in 100 mL of buffer solution containing: 0.6 g glycine, 0.2 g sodium acetate, 0.3 g sodium chloride, and ~5 mg Polysorbate 80. Immunoglobulin G purity reaches 100%, the pH is in the range of 4.8 to 5.0, and osmolality is not less than 240 mOsmol/kg (typically 420 to 500 mOsmol/kg). The immunoglobulins present are virtually 100% IgG, and the distribution of the four IgG subclasses is approximately 62% IgG1, 31% IgG2, 6% IgG3, and 1% IgG4. The content of IgA is lower than 10 µg/mL. The Anti-D content of the final product is monitored and controlled to specification [18].

In a preclinical study in male Wistar rats, some small, but statistically significant, hypertensive differences were seen in the GAMMAPLEX group when compared with the vehicle control group after 140 minutes. These differences were not seen in another study when the product was infused at a lower rate; it was concluded that the rise in blood pressure with GAMMAPLEX in the first study was due to infusion rate, the total dose of IgG infused, or both. Furthermore, the

infusion rates used in these nonclinical studies convert to a clinical rate of 0.07-0.1 mL/kg/min. The recommended starting rate for the infusions in subjects receiving GAMMAPLEX is 0.01-0.02 mL/kg/min, so hypertension should not be an issue in clinical studies [19].

GAMMAPLEX 400 mg/kg IGIV given at up to 6 mL/min was well tolerated in a single-dose pharmacokinetics (PK) study in 36 healthy volunteers. No SAEs were reported [20].

### **3.2. Benefit/Risk Statement**

ITP is potentially fatal mainly because of the risk of intracranial hemorrhage. Other bleeding may occur and may result in acute or chronic anemia. The use of IGIV to rapidly increase platelet count has been shown in other studies to decrease signs and symptoms of bleeding/hemorrhage and may obviate or delay the need for splenectomy. Splenectomy carries an intraoperative risk of hemorrhage and the long term risk to the patient of infections (especially pneumococcal) as well as failure to permanently increase platelet counts.

Most of the IGIV used in the U.S. is for off-label indications, such as peripheral neuropathy and other autoimmune diseases. In addition, there have been several mergers of manufacturers of IGIV, resulting in fewer products on the market. Although the manufacturers have generally kept up with the demand for IGIV, these changes in the marketplace have resulted in disruption in the supply of different products at different times. Changes in products may result in an increased frequency of adverse events (AEs) in patients who previously tolerated a given preparation [19]. For this reason, entry of additional manufacturers into the U.S. market (and potentially other markets) may help to provide a steady stream of consistent products for ITP patients.

The European Medicines Agency (EMA) regards ITP as a good model for other conditions with a known or presumed immunological pathogenesis, because this condition tests out the integrity/activity of the Fc structure of the IgG molecule.

As with any blood product, viral safety is a concern. GAMMAPLEX undergoes a stringent multi-step process, including solvent/detergent treatment, nanofiltration and a terminal low pH incubation of the finished product, to reduce the risk of potential viral contaminants and enhance the safety of the product [19].

IGIV products have been associated with renal AEs, particularly in those products containing sucrose as a stabilizer. GAMMAPLEX contains sorbitol as a stabilizer, thereby reducing the risk of such reactions.

## **4. STUDY OBJECTIVES**

### **4.1. Primary Objective**

The primary objective is to determine if BPL's GAMMAPLEX raises the platelet count of subjects with chronic ITP to a threshold of  $50 \times 10^9/L$ , similar to that of a historical control [9-17,21].

### **4.2. Secondary Objective**

The secondary objectives are:

- To determine the safety of GAMMAPLEX at the dose used in this study.

- To determine if GAMMAPLEX maintains platelet counts of  $\geq 50 \times 10^9/L$  in subjects with chronic ITP for a period of time similar to that of a historical control [9-17,21].

## **5. STUDY DESIGN**

### **5.1. Study Administration**

#### **5.1.1. Primary Investigator**

The primary investigator at each site is responsible for all functions performed at their site as a part of this study. Qualified personnel who also perform protocol-defined functions will be identified in a Study Personnel Signature Log that will be maintained at each site.

#### **5.1.2. Contract Research Organization**

The contract research organizations (CROs) in this study are:

#### **5.1.3. Central Laboratory**

All samples for laboratory tests should be shipped to the selected central laboratory in each country for the study, as described in the Laboratory Manual.

#### **5.1.4. Distributor/Central Pharmacy**

Study product will be exported to and will be stored by the selected central distributor/pharmacy in each country and will be distributed to the investigator site as described in the Pharmacy Manual.

#### **5.1.5. Sample Storage Facility**

Retention samples (see Section 9.3.1) will initially be shipped from the investigator site to the central laboratory, as detailed in the laboratory manual. Those samples will later be shipped by the central laboratory to Cryo-store, [name], for long-term storage.

### **5.2. Overall Study Design**

This will be a multicenter, open-label study conducted at approximately 25 clinical sites in the U.S., India, and Argentina. A minimum of 31 evaluable subjects will be enrolled in the study.

The final number will depend on the number estimated by the power calculation in the partial analysis.

After screening and enrollment, subjects will initially receive infusions of GAMMAPLEX on Days 1 and 2 (first treatment course). Subjects will be assessed for safety and efficacy on Days 3, 5, 9, 14, 21, and 32; then they will then return for a final follow-up visit (End of Study), to include viral safety tests on Day 90.

If the platelet count is not maintained for the desired length of time after the first course of GAMMAPLEX, and at the discretion of the study investigator and subject/guardian, subjects may receive up to 2 additional courses of GAMMAPLEX within the 32 to 90 days after the first dose. Subjects who receive additional treatments will attend all safety and efficacy follow-up visits as scheduled for the first treatment course. In addition, they will be assessed for safety prior to each additional dose of GAMMAPLEX and 3 days after the end of each treatment course. All subjects will attend one End of Study visit, which will be 90 days, approximately 3 months, after the first infusion of the last course of GAMMAPLEX (see Section 5.3.1.6).

Efficacy data will be collected and analyzed for the first course of GAMMAPLEX only.

### 5.3. Study Visits

The study visits are summarized in the study flow chart (Figure 1). The schedule of assessments is in Table 1, and in Table 2 for subjects who receive additional treatment courses. The study visits are identified as follows:

- Screening visit (can occur up to 6 months prior to Day 1)
- Visit(s) to check platelet count, (if applicable) – for those subjects whose platelet count is above  $20 \times 10^9/L$  at the screening visit, samples can be sent to the local laboratory to check the platelet count. For subjects screened more than 14 days prior to Day 1, additional safety laboratory samples will be analyzed by the local laboratory e.g. CBC, LFTs, serum Creatinine/BUN.
- First course of GAMMAPLEX – there will be 2 infusion visits on consecutive days (Days 1 and 2)
- Follow-up – 6 follow-up visits from Day 3 to Day 32
- Second and third courses of GAMMAPLEX – at the discretion of the investigator, subjects may receive 1 or 2 more courses of GAMMAPLEX within the period 32 to 90 days following the first course of GAMMAPLEX. Each course will consist of 2 infusions on consecutive days and will be scheduled at an appropriate time following the first treatment course, depending upon the subject's response to the previous treatment course of GAMMAPLEX
- End of Study visit – For all subjects this visit will be approximately 3 months after the first infusion of the last course of GAMMAPLEX and will be the End of Study visit for all subjects irrespective of whether they received 1, 2, or 3 courses. For subjects receiving 1 treatment course of GAMMAPLEX only, this visit will take place on Day 90.

### **5.3.1. Description of Study Visits**

#### **5.3.1.1. Screening Visit**

##### *Subject Eligibility*

The subject's eligibility to participate in the study will be assessed at this visit according to the inclusion and exclusion criteria. This visit can occur up to 6 months prior to Day 1.

##### *Informed Consent*

Written informed consent must be obtained from the subject by qualified personnel and signed by the investigator before any study procedures, including screening laboratory tests, are carried out (see Section 11.3). Informed consent can be taken up to 6 months prior to Day 1.

##### *Pregnancy Test*

All female subjects of childbearing potential will receive a urine-based, human chorionic gonadotrophin (HCG) pregnancy test irrespective of claimed inability to conceive.

##### *Complete Medical History*

A complete medical history will be obtained from each subject at this visit. The history will specifically include documentation of the diagnosis of chronic ITP, the reason why other causes of thrombocytopenia were excluded, general medical history, history and outcome of previous use of and/or reactions to any IGIV or other blood product, history and treatment of ITP, and history of bleeding/hemorrhage. Bone marrow examination is not required, but if it has been done, it should be consistent with ITP with, for example, normal or increased megakaryocytes. For subjects who have had bone marrow examinations, the date and findings should be recorded on the Case Report Form (CRF) at the time of screening.

The medical history must include the use of previous IGIV treatments received; the product name, the unit dose, and how they were tolerated must be recorded. The previous use of an IGIV product must be documented in the subject's CRF. In addition the treatment regimen and dose of corticosteroids, azathioprine, cyclophosphamide, and attenuated androgens must be documented in the subject's CRF.

##### *Physical Examination*

Physical examination will be performed by appropriately qualified personnel. The physical examination is also a safety variable (see Section 9.5.).

##### *Vital Signs*

Vital signs assessed by qualified personnel will be entered on the CRF. The vital signs to be observed will be diastolic and systolic blood pressure (mmHg), pulse rate (beats/min), respiration rate (breaths/min), and oral temperature (°C). The subject must be in the same position each time vital signs are obtained. The vital signs are also a safety variable (see Section 9.2.).

*Blood Samples for Laboratory Tests*

Blood samples will be obtained for Laboratory A and Laboratory B (Clinical Laboratory tests are a safety variable, see Section 9.3). If a subject is otherwise eligible, but the platelet count is greater than  $20 \times 10^9/L$ , the subject will not be enrolled. If at a subsequent visit (within 6 months of the screening visit) the subject's clinical condition suggests to the investigator that their platelet count may have dropped, the subject may have their platelet count re-measured by the local laboratory. If the platelet count is  $\leq 20 \times 10^9/L$ , the general health of the subject has not significantly changed, and no changes in concomitant medications or treatment have occurred which would violate the inclusion criteria, then safety blood samples should be measured by the local laboratory e.g. CBC, LFTs, serum Creatinine/BUN. If these all meet the entry criteria then the subject can be considered as eligible, and can be immediately enrolled in the study.

*Other Blood Samples*

The following additional samples will be collected:

- Serum for IgG, IgA, and IgM levels
- A reserve sample (see Section 9.3.1)
- A sample for a Direct Coombs' test (see Section 9.3.2).
- NAT for HCV, HIV and Parvovirus B19
- Serology for HIV1 and HIV2, HCV, HBsAg
- Blood typing (A, B, O, Rh(D)+/-)

*Urinalysis*

A urinalysis with microscopic examination will be done as a part of this visit.

*Assessment for Bleeding/Hemorrhage*

The subject will be assessed for bleeding and hemorrhage; this will be graded as detailed in Appendix 1 and recorded on the subject's CRF.

*Concomitant medications*

If the subject is enrolled within 14 days of screening, all medications the subject is taking at the time of screening may be continued through the completion of the second infusion, including corticosteroids; however, the dose must remain unaltered through Day 9 unless some condition of the subject requires a change. If possible, doses of corticosteroids or other immunosuppressant medications should remain constant until Day 32 (see Section 6.1). All concomitant medications will be recorded on the CRFs.

If the subject is not enrolled within 14 days of screening, it should be noted that doses/regimen of corticosteroid must have been stable for 2 weeks prior to Day 1; and doses/regimen of azathioprine, cyclophosphamide, and attenuated androgens must have been stable for 2 months prior to Day 1. Changes to the dosage of these medications should be avoided as mentioned above. In addition subjects are not to receive an IGIV preparation or an investigational agent or

any blood, blood product or blood derivative within 1 month prior to Day 1, and receipt of any live virus vaccine and Rituximab is not allowed within 3 months prior to Day 1.

Administration of corticosteroids to decrease adverse reactions to the infusion may not be given before the IGIV infusions. However, pre-medication with analgesic or antihistamine drugs is permissible if required.

No blood products, including IGIV (other than GAMMAPLEX in accordance with the protocol), may be given during the study until the End of Study visit (viral safety visit approximately 3 months after the last dose of GAMMAPLEX).

#### **5.3.1.2. Infusion Visits for First Treatment Course (Days 1 and 2)**

At these visits, the following will be done:

##### *Eligibility and Enrollment*

For subjects screened more than 14 days prior to Day 1, in addition to the sample taken to check the platelet count, blood samples for safety assessment by the local laboratory should be taken to ensure there have been no further changes in a subject's safety profile since screening, e.g. CBC, LFTs, serum Creatinine/BUN.

On Day 1 only, a sample for platelet count will be analyzed locally before the first infusion to ensure that the subject's platelet count is  $\leq 20 \times 10^9/L$  and that they are still eligible to enter the study.

The subject's eligibility to participate in the study will be confirmed only on Day 1. If eligible, the subject will be assigned a subject number. Subject numbers will be assigned as indicated in the Data Entry Instructions.

Samples for Laboratory A and B will be taken for testing by the central laboratory prior to infusion with GAMMAPLEX on Day 1 only. Eligibility to be included in the efficacy analysis will only be confirmed once the safety laboratory results are returned from the central laboratory.

##### *Pregnancy Test*

A urine-based HCG test will be done before the infusion with GAMMAPLEX on Day 1.

##### *Interval Medical History*

An interval medical history will be performed before each infusion. Any changes from screening will be recorded on the CRF.

##### *Physical Examination*

A physical examination will be performed before each infusion and the results recorded on the CRF.

##### *Vital Signs*

At each infusion visit, vital signs will be assessed by qualified personnel and entered in the CRF.

Vital signs will be recorded at the following times:

- 10 minutes before, and at the start of each infusion (to have 2 baselines)
- 10 minutes after initiation of the infusion, and 10 minutes after each rate increase
- 10 minutes and 30 minutes after the maximum rate is achieved, and every 60 minutes thereafter until the infusion is stopped
- the time at which each infusion is stopped
- 15 and 30 minutes after stopping each infusion

**Before listing changes in vital signs as AEs, each change should be assessed for clinical relevance (see Sections 9.1.1.2 and 9.2).** If AEs occur, vital signs will be monitored more frequently, as appropriate.

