#### *Assessment for Bleeding/Hemorrhage*

At each visit, the subject will be assessed for bleeding and hemorrhage; this will be graded as detailed in Appendix 1 and recorded in the subject's CRF (along with any bleeding episodes recorded in the subject's diary card).

*Concomitant medications*

All concomitant medications, including any entries on the diary cards, must be recorded in the subject's CRF including corticosteroids and immunosuppressants, if applicable (see also Section 5.3.1.1).

*Diary Card*

Each subject will be provided with a diary card at the first infusion visit. Subjects will be instructed to complete a diary entry every day from Day 1 until Day 32 describing any AEs and concomitant medications. Subjects should also document in their diaries any bleeding episodes, or the absence of such episodes, every day.

At each visit from Day 1 to Day 32, the study nurse will review the diary cards, and details of AEs, bleeding episodes, and concomitant medications will be entered in the subject's CRF. The study nurse will collect diaries at the Day 32 follow-up visit.

*GAMMAPLEX Infusion*

Each subject will be treated with GAMMAPLEX at a total dose of 2 g/kg body weight divided over 2 consecutive days (i.e., 1 g/kg on Day 1 and 1 g/kg on Day 2). IGIV will be infused by means of an infusion pump for precise infusion rates. (See Section 7.2 for details on treatment, dosing, and administration).

At the discretion of the investigator, if the subject is capable, he/she will be allowed to leave the study center after the completion of the assessment 60 minutes after the infusion.

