#### **5.3.1.4. Infusion Visits for Additional Treatment Course(s) (Infusions 3–6)**

Additional treatment courses are not mandatory, but they can be considered if the platelet count drops below  $25 \times 10^9/L$ . If the study physician/investigator deems it necessary on clinical grounds to give the IGIV during the period 32 to 90 days following the first treatment course, he/she, at his/her discretion, may give another 1 or 2 courses of GAMMAPLEX (treatment courses 2 and 3). See Figure 1 and Table 2.

If, however, it is considered that a second course of GAMMAPLEX would be appropriate after Day 9 and before Day 32, investigators must discuss this with the medical monitor and sponsor before proceeding. The administration of GAMMAPLEX during this period would interfere with the analysis of the duration of effect of GAMMAPLEX, an important secondary efficacy variable.

Before the first infusion of GAMMAPLEX in each additional treatment course, the following will be done (as detailed in Section 5.3.1.2):

*Interval Medical History**Physical Examination**Vital Signs**Blood Samples for Laboratory Tests*

The following samples will be taken before dosing on the first day of the treatment course only

- Platelet count (local laboratory)
- Blood for Laboratory B

Samples for Laboratory A will be collected at each infusion visit.

*Direct Coombs' Test before the first infusion of each treatment course (see Section 9.3.2)*

*Reserve sample before the first infusion of each treatment course. (See Section 9.3.1)*

*Urinalysis before the first infusion of each treatment course*

*GAMMAPLEX Infusion*

Each subject will be treated with GAMMAPLEX at a total dose of 2 g/kg body weight divided over 2 consecutive days, i.e., 1 g/kg on Day X and 1 g/kg on Day X+1 (see Sections 5.3.1.2 and 7.2). The date of additional treatment courses will be decided by the investigator based upon the subject's response to the first treatment course (for the second treatment course) and the second treatment course (for the third treatment course).

*Adverse Events**Concomitant medications***5.3.1.5. Follow-Up Visits for Additional Treatment Course(s) (Infusions 3–6)**

Subjects will return for a follow-up visit 3 days after the end of each of the second and third treatment courses, if they receive them (Day X+4 and Day Y+4 respectively). At those visits, the following will be done (see Section 5.3.1.2 and Table 2):

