## Bio Products Laboratory

## CONFIDENTIAL

- b) Vital Signs (blood pressure, heart rate, oral temperature, respiratory rate) should be taken as follows: 10 min before and at the start of each infusion, 10 min after initiation of each infusion, 10 min after each rate increase, 10 min and 30 min after maximum rate is achieved, every 60 minutes until infusion is complete, at the time the infusion stopped, and 15, and 30, after the infusion has stopped. Vital signs must be taken with the subject in the same position on each occasion.
- c) On Day 1 (and visit(s) to check platelet count, if applicable) only, a platelet count will also be done locally prior to infusion to confirm eligibility of the subject (2mL).
- d) For all subjects screened more than 14 days prior to Day 1, additional safety laboratory samples will be taken to be analyzed by the local laboratory e.g. CBC, LFTs, serum Creatinine/BUN.
- e) Laboratory A includes CBC with differential and platelet count.
- f) Laboratory B includes bilirubin, creatinine, BUN, ALT, AST.
- g) Director Coombs' Test - on Days 5 and 14, samples for LDH, haptoglobin, and urine hemosiderin will also be taken.
- h) NAT for HCV, HIV, and Parvovirus B19.
- i) Parvovirus B19 only will be tested on Day 9; 4-mL blood sample.
- j) Serology for HIV 1 & 2, HCV and HBsAg. **Note: If a positive result on an NAT or serologic test occurs, it will be repeated at the subject's next scheduled visit.**
- k) Immunoglobulins - IgG (all visits) and IgA and IgM (Screening and at End of Study visit only).
- l) The 1-mL sample needed for blood typing will come from the tube taken for the Direct Coombs' Test.
- m) For all subjects this visit will be approximately 3 months after the last dose of GAMMAPLEX and will be the End of Study visit for all subjects irrespective of whether they received 1, 2, or 3 courses. For subjects receiving 1 treatment course of GAMMAPLEX only, this visit will take place on Day 90.

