a) Vital Signs (blood pressure, heart rate, oral temperature, respiratory rate) should be taken 10 min before and at the start of each infusion, 10 min after initiation of each infusion, and 10 min after each rate increase, 10 min and 30 min after maximum rate is achieved, and every 60 minutes until infusion is complete, at the time the infusion stopped, and 15, 30 and 60 min after the infusion has stopped. Vital signs must be taken with the subject in the same position on each occasion.

b) Laboratory A includes CBC with differential and platelet count. \*Note: On Day 1 only, a platelet count will also be done locally prior to infusion to confirm eligibility of the subject (2mL).

c) Laboratory B includes bilirubin, creatinine, BUN, ALT, AST.

d) Direct Coombs' Test - on Days X+4 and Y+4, samples for LDH, haptoglobin, and urine hemosiderin will also be taken.

e) NAT for HCV, HIV, and Parvovirus B19.

f) Serology for HIV 1 & 2, HCV and HBsAg. Note: If a positive result on an NAT or serologic test occurs, it will be repeated at the subject's next scheduled visit.

g) Immunology - IgG, IgA, and IgM on 3-month viral safety visit only.

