#### *AEs Occurring During the Infusion and up to 60 minutes from the End of Infusion*

The severity of AEs that occur during or less than 60 min after an infusion will be graded according to the criteria in Table 4.

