#### *AEs Occurring Later than 60 minutes After the End of Infusion*

The severity of AEs that occur more than 60 min after the end of an infusion will be graded as follows:

- **Mild:** Event resolved spontaneously or no treatment was necessary beyond administration of non-prescription drugs.
- **Moderate:** Event required use of prescription drugs and produced no sequelae.
- **Severe:** Event produced sequelae or required a visit to health care professional.

**Table 4 Criteria for Grading Severity of Infusion-Related Adverse Eventsa that Occur During Infusion or up to 60 minutes from the End of Infusion**

| TYPE OF EVENT
Sign/Symptom                                                                                                                                     | Mild                                                   | Moderate                                                                                                     | Severe                                                                                                                                        |
|-------------------------------------------------------------------------------------------------------------------------------------------------------------------|--------------------------------------------------------|--------------------------------------------------------------------------------------------------------------|-----------------------------------------------------------------------------------------------------------------------------------------------|
| CARDIOVASCULAR                                                                                                                                             |                                                        |                                                                                                              |                                                                                                                                               |

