### **9.2. Vital Signs**

Vital sign values will be obtained as detailed in Section 5.3.1.2. Any clinically significant changes in vital signs will be reported as AEs as described in Section 9.1.1.2. Clinically significant hypotension (i.e., a  $\geq 30$  mmHg drop in systolic blood pressure accompanied by clinical findings/symptoms, or a systolic blood pressure of  $\leq 70$  mmHg) and/or anaphylactic reactions (significant hypotension with generalized hives/angioedema or bronchospasm) warrant discontinuation of the infusion and administration of appropriate supportive care as deemed necessary by the investigator (may include epinephrine, antihistamine, corticosteroids, supplemental oxygen, expansion of the plasma volume as necessary, etc.). These occurrences must be recorded in the CRF as AEs. At the discretion of the investigator, the subject may be withdrawn from the study, but will complete the follow-up visits. Before listing changes in vital signs as AEs, each change should be assessed for clinical relevance.

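### Scheduled first-course vital signs end 30 minutes after infusion, although discharge, Table 4 grading and the later-course schedule all run to 60 minutes

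*Protocol*

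**What the plan says.** Two places give the first-course schedule, and they agree. The Vital Signs list in Protocol Section 5.3.1.2 ends with readings at "15 and 30 minutes after stopping each infusion". Table 1 footnote b has "15, and 30, after the infusion has stopped".

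Four other places bear on the same hour:

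- **Discharge.** The infusion paragraph of Section 5.3.1.2 lets a capable subject leave, at the investigator's discretion, "after the completion of the assessment 60 minutes after the infusion". Neither that section nor Table 1 says what this assessment consists of.
- **Severity grading.** Section 9.1.1.2 applies Table 4 to "AEs that occur during or less than 60 min after an infusion". The table's title and its footnote a say up to 60 minutes. A different scale, based on treatment needed and sequelae, takes over after that: "The severity of AEs that occur more than 60 min after the end of an infusion will be graded as follows".
- **Later courses.** Table 2 footnote a sets readings at "15, 30 and 60 min after the infusion has stopped" for infusions 3 to 6.
- **Safety section.** Section 9.2 states: "Vital sign values will be obtained as detailed in Section 5.3.1.2". It does not restrict this to the first course.

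**The concern.** Three provisions treat 60 minutes as the end of the immediate post-infusion period: the discharge rule, the Table 4 window and the later-course schedule. The first-course vital-sign list alone stops at 30 minutes, and no reason is given. The shorter schedule applies to the mandatory course, which is each subject's first exposure to the product in this study. The longer one applies to optional courses in subjects who have already received it.

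At stake is the capture of safety data. A site following Section 5.3.1.2 and Table 1 to the letter may discharge a subject after a 60-minute assessment that included no measurement of blood pressure, pulse, respiration or temperature. A change without symptoms that began after the 30-minute reading would then not be seen before the subject left.

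**Working it through.** The protocol states no figure to reproduce. The check compares the texts and makes a few counts.

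**Last scheduled post-infusion reading**

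| Source | Applies to | Readings after stopping | Last |
|---|---|---|---|
| Section 5.3.1.2 | Infusions 1–2 | 15, 30 min | 30 min |
| Table 1 footnote b | Infusions 1–2 | 15, 30 min | 30 min |
| Table 2 footnote a | Infusions 3–6 | 15, 30, 60 min | 60 min |
| Section 9.2 | Not limited to a course | Refers to 5.3.1.2 | 30 min |

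No first-course visit has two competing schedules. The gap lies inside Section 5.3.1.2, between its vital-sign list (30 minutes) and its discharge rule (60 minutes). Separately, the list that Section 9.2 names lacks the 60-minute reading that Table 2 requires.

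**Part of the Table 4 window after the last reading**

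(60 − 30) / 60 = 50% of the post-infusion window. This describes the current schedule only. One added reading at 60 minutes would check the end of the interval and would not monitor the time between.

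**Table 4 rows that use a measured vital sign**

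- Total rows: 4 cardiovascular + 1 allergic + 6 systemic = 11.
- Rows using a vital-sign value: tachycardia (heart rate relative to baseline), hypotension and hypertension (percentage change from pre-infusion pressure), allergic (tachypnea relative to baseline) and fever (temperature) = 5 of 11.

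**Infusions without a scheduled 60-minute reading**

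- One course: 2 of 2.
- Two courses: 2 of 4.
- Three courses: 2 of 6.
- Minimum of 31 evaluable subjects: 2 × 31 = 62 infusions. This is a lower bound, because subjects excluded from efficacy but kept for safety are infused as well.

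**Which changes the added reading would find**

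- Present at 30 minutes: already found under the current schedule.
- Begins after 30 minutes and is still present at 60: not measured now unless it causes symptoms or the site chooses to measure; would be found.
- Begins after 30 minutes and resolves before 60: missed now and still missed.

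The gain is confined to the second group.

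**The case against.** The strongest reply is that the first-course schedule is internally consistent, observation to 60 minutes is already required, and one more reading is a matter of preference. Much of this stands:

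- The subject stays until the 60-minute assessment, and vital signs are taken more often if an AE occurs. That rule, however, starts only once something has been noticed.
- A change that persists meets later readings: two baselines before the Day 2 infusion, and vital signs on Days 3, 5 and 9.
- Table 4 footnote b lets the investigator class a blood-pressure change as physiologic if heart rate has not risen and the subject is comfortable or asleep. Sections 5.3.1.2 and 9.2 ask for a clinical-relevance check before a change is listed as an AE. This reduces what an isolated pressure finding would add. It does not cover isolated tachycardia, and the judgment itself needs pressure and heart rate to have been measured.
- Once the maximum rate is established, the protocol accepts readings 60 minutes apart, so a 30-minute gap is not unusual in itself. The weakness is that nothing is specified at the time point on which discharge depends.
- The 60-minute assessment may have been meant to include vital signs. If so, the change only writes that down.

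A reader might also infer more than the text supports:

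- *That a change missed before 60 minutes can no longer be graded on Table 4.* Section 9.1.1.2 chooses the scale by when the event occurs, not when it is recorded. Later events are still graded, and all AEs to 72 hours are recorded as infusion-related.
- *That the unequal schedules spoil a comparison between courses.* Section 10.4.2 plans summary statistics and change from baseline for vital signs. No comparison between courses is planned.
- *That Section 5.3.1.4 imposes the 30-minute schedule on later courses.* Its pointer "see Sections 5.3.1.2 and 7.2" sits in the infusion paragraph and concerns dosing. Its other reference to 5.3.1.2 introduces procedures done before the first infusion of a course. Section 5.3 sends later courses to Table 2. The mismatch for later courses therefore rests on Section 9.2 alone.

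**Conclusion.** The point holds as a cheap improvement to safety monitoring. The last scheduled vital signs in the first course precede the 60-minute discharge assessment by 30 minutes, and the protocol does not say what that assessment contains. A symptom-free change that begins after the 30-minute reading and is still present at 60 minutes can go unmeasured before discharge. This applies to both infusions of the mandatory course, at least 62 infusions for 31 evaluable subjects.

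The conclusion assumes that sites follow Section 5.3.1.2 and Table 1 as written and do not read vital signs into the undefined assessment. The documents give no frequency for such changes, so the number likely to be missed cannot be estimated. No harm is demonstrated, and neither the primary nor the secondary efficacy analyses are affected.

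**What to change.** In Section 5.3.1.2 and Table 1 footnote b, set post-infusion vital signs at 15, 30 and 60 minutes for each infusion, as Table 2 footnote a already does. State in the infusion paragraph of Section 5.3.1.2 that the 60-minute assessment before discharge includes these vital signs. Section 9.2 can stay as it is, because it will then point to one schedule that is right for all courses.

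The cost is one extra non-invasive reading per first-course infusion (2 per subject, about 62 for 31 subjects) and a matching CRF field. The subject is already held for assessment at that time, so no extra visit, blood sample or waiting time is needed.
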